## Abstract

**Background:**

The United States faces a nursing shortage driven by a burnout epidemic among nurses and nursing students. Nursing students are an integral population to fuel the nursing workforce at high risk of burnout and increased rates of perceived stress.

**Objective:**

The aim of this paper is to describe WellNurse, a holistic, interdisciplinary, multidimensional longitudinal research study that examines evidence-based interventions intended to reduce burnout and increase resilience among graduate and undergraduate nursing students.

**Methods:**

Graduate and undergraduate nursing students matriculated at a large public university in the northeastern United States are eligible to enroll in this ongoing, longitudinal cohort study beginning in March 2021. Participants complete a battery of health measurements twice each semester during the fourth week and the week before final examinations. The measures include the Perceived Stress Scale, the Satisfaction with Life Scale, the Oldenburg Burnout Inventory, the Brief Resilience Scale, and the Pittsburgh Sleep Quality Index. Participants are eligible to enroll in a variety of interventions, including mindfulness-based stress reduction, mindful eating, fitness training, and massage therapy. Those who enroll in specific, targeted interventions complete additional measures designed to target the aim of the intervention. All participants receive a free Fitbit device. Additional environmental changes are being implemented to further promote a culture that supports academic well-being, including recruiting a diverse student population through evidence-based holistic admissions, inclusive teaching design, targeted resilience and stress reduction workshops, and cultural shifts within classrooms and curricula. The study design protocol is registered at Open Science Framework (DOI 10.17605/OSF.IO/NCBPE).

**Results:**

The project was funded on January 1, 2022. Data collection started in March 2022. A total of 267 participants have been recruited. Results will be published after each semester starting in December 2023. WellNurse evaluation follows the Rapid Cycle Quality Improvement framework to continuously monitor ongoing project processes, activity outcomes, and progress toward reducing burnout and increasing resilience. Rapid Cycle Quality Improvement promotes the ability to alter WellNurse interventions, examine multiple interventions, and test their effectiveness among the nursing education population to identify the most effective interventions.

**Conclusions:**

Academic nursing organizations must address student burnout risk and increase resilience to produce a future workforce that provides high-quality patient care to a diverse population. Findings from WellNurse will support evidence-based implementations for public baccalaureate and master’s nursing programs in the United States.

**International Registered Report Identifier (IRRID):**

DERR1-10.2196/49020

## Introduction

### Background

The COVID-19 pandemic exacerbated already prominent feelings of burnout and stress among nursing students in the United States. Nursing students experienced high levels of perceived stress elicited by numerous interpersonal, intrapersonal, and community factors [1]. Nursing students’ stress contributes to less academic engagement [2], and over 55% of nursing students report increased stress and worsened health after entering nursing school [3]. During the COVID-19 pandemic, economic strain, academic workload, and isolation from peers accelerated nursing students’ stress and well-being [4]. Students cite limited clinical experiential learning and adjustment to web-based learning as prominent barriers influencing their intention to join the nursing workforce [4]. McKee-Lopez et al [5] found that adverse childhood experiences also contribute to mental health status among the nursing population, with nursing students experiencing a higher prevalence of adverse childhood events. Adverse childhood events have been associated with higher rates of burnout and depression among undergraduate nursing students [5]. Urban et al [6] found that nursing undergraduate students reported significantly higher stress levels than their nonnursing major peers. Moreover, COVID-19 can be seen as an adverse experience faced by all new incoming nursing students. A total of 60% of nurses younger than 35 reported an emotional, traumatic, or stressful event related to COVID-19 [7]. Nursing students are a critical component of the future nursing workforce. Currently, 55% of the nursing workforce experiences symptoms of burnout [8], contributing to an alarming acceleration of nurse turnover and shortages nationally. Stress does, in fact, predict nurses’ job satisfaction and turnover intention [9]. In total, 25% of nurses left the profession in 2022 compared with 20% in 2020, and the average hospital turned over 95% of its nursing staff in the past 5 years [10].

Personal resilience, or the capacity to adjust positively to adversity to limit negative impacts, has been correlated with reduced burnout [6]. As the United States faces a critical shortage of nurses confounded by high rates of burnout and stress, nursing schools must develop interventions and strategies to reduce burnout and promote resilience among nursing students. Stress reduction interventions could promote improved stress management and mitigate burnout among students [2,3,11], which can support nursing student retention, on-time graduation, and resilience when students transition to the nursing workforce.

The health care profession’s burnout crisis prompted the National Academy of Sciences to convene a committee and create a report that promotes the collective urgency to address burnout and resilience among health professionals, including nurses and students. Their vision includes a thriving health care workforce that provides high-quality care to patients in an environment that fosters their well-being [8]. The research study and project presented in this paper align with five of the seven priorities outlined by the academy: (1) create and sustain positive work and learning environments and culture; (2) invest in measurement, assessment strategies, and research; (3) support mental health and reduce stigma; (6) institutionalize well-being as a long-term value; and (7) recruit and retain a diverse and inclusive health workforce. There is a lack of substantive research that applies longitudinal analysis, large sample sizes, or randomization to support effective interventions that reduce burnout and promote resilience among nursing students [12], which this study aims to address.

WellNurse (Wellness in Nursing Education to Promote Resilience and Reduce Burnout) is a longitudinal research study implemented at a public nursing school in the northeastern United States to reduce burnout and increase resilience among nursing students. This multidimensional study examines the effect of various interventions on burnout, resilience, perceived stress, and academic performance. This paper aims to describe the comprehensive and holistic interventions and measures provided to nursing students at a public university in the northeast offering BSN and MSN education.

### WellNurse Project Goals

The project’s overarching purpose is to reduce burnout and increase resilience among nursing students at a public university in the northeast. Several objectives were implemented to achieve this aim, including (1) providing access to evidence-based mindfulness-based stress reduction (MBSR) to nursing students, faculty, and staff within a 3-year time frame; (2) providing evidence-based physical fitness, nutritional, and peer mentor training and support to all nursing students, faculty, and staff; (3) establishing a resilience and stress management curriculum to sustain program activities after the grant period with a credit-bearing course; and (4) creating an environment and culture that embraces resilience, wellness, diversity, equity, and inclusion. The study design protocol is registered at Open Science Framework [13].

## Methods

### Participant Recruitment

Matriculated graduate and undergraduate nursing students, faculty, and staff older than 18 years who complete a web-based consent form are eligible to participate in the study. The initial phase of the study occurred from March to May 2022, and recruitment is ongoing as new students and faculty will enter the program through December 2024.

The recruitment strategy involves the WellNurse research team visiting various in-person and remote nursing classes and hosting meetings with administrative staff and faculty. The team also posts recruitment messages on the school’s social media pages. Participants are offered a free Fitbit and enrollment in various interventions described below and can choose whether or not they consent to the evaluation aspect of the project. Some academic courses provide course credit, extra credit, or clinical hours to students who agree to participate. Faculty and staff are provided work time to participate in the interventions.

### Measures

#### Comprehensive Wellness Survey

After completing a web-based consent form, participants complete a comprehensive health behavior survey. This survey is distributed during week 4 and again during week 14 (the week before finals week) in the fall and spring semesters. Week 4 was selected based on the typical nursing student’s academic loads and stress. Examinations and competency testing begin each semester’s third to fourth week, accelerating stress during those periods. Participants complete the comprehensive health behavior survey during designated class or work time. Additional measures are collected before specific engagement in targeted study interventions. Participants’ answers are tracked through the project using unique ID codes. As listed below, several variables are assessed to capture the health of nursing students. The comprehensive measurement strategy aligns with Priority Area 2 from the National Academy of Sciences [8], which recommends the longitudinal use of valid and reliable measurements of burnout and factors that mitigate burnout to drive effective interventions and data-driven decision-making at the organizational level.

##### Demographics

Participants are asked several sociodemographic questions, including gender identity, sexuality, and ethnicity. Participants also provide their grade point average. Student progression status is also tracked to determine how various interventions influence retention and on-time graduation.

##### Perceived Stress Scale

The Perceived Stress Scale (PSS) is used to measure perceived stress. The scale includes 10 items that address experiences of distress related to “how unpredictable, uncontrollable, and overloaded respondents find their lives” [14]. Example items include “In the last month, how often have you felt that you were unable to control the important things in your life?” and “In the last month, how often have you felt difficulties were piling up so high that you could not overcome them?” The PSS demonstrates reliability and validity among healthy college populations [14].

##### Satisfaction With Life Scale

The Satisfaction with Life Scale is used to measure satisfaction with life. The 5-item Satisfaction with Life Scale [15] uses Likert scale responses ranging from “strongly agree” to “strongly disagree.” An example item is “The conditions of my life are excellent.” The measure demonstrates strong validity and reliability in past research [16,17].

##### Oldenburg Burnout Inventory

The Oldenburg Burnout Inventory is a 16-item measurement tool that measures the concepts of disengagement and exhaustion to assess burnout. Participants rank statements such as “When I work, I usually feel energized,” with Likert responses ranging from “strongly agree” to “strongly disagree.” The Oldenburg Burnout Inventory is a valid and reliable measure of burnout related to work and academics [18].

##### Brief Resilience Scale

The Brief Resilience Scale is a 6-item scale that measures resilience and one’s ability to bounce back and recover from stress. The Brief Resilience Scale is a valid and reliable measure of resilience [19].

##### BMI

BMI screens for weight categories that may be associated with health problems and reflects a person’s weight in kilograms divided by the square of height in meters [20]. Participants were asked to self-report their height and weight, and a BMI for each participant was derived accordingly.

##### Pittsburgh Sleep Quality Index

Sleep quality is measured using the 2-item Pittsburgh Sleep Quality Index [21], which assesses participants’ estimated average hours of sleep per night and overall perception of sleep quality within the past 7 days. This survey has demonstrated acceptable validity and reliability in past research [21].

#### Nutrition Assessments

WellNurse participants have an opportunity to engage in a mindful eating cooking workshop conducted by a registered dietitian nutritionist. Before attendance, participants are required to complete a web-based registration form and relevant assessments. The assessments involve multiple health and nutrition behavior surveys, described below.

##### Mindful Eating Questionnaire

The Mindful Eating Questionnaire was developed to measure mindful eating, which can be described as nonjudgmental awareness of physical and emotional sensations associated with eating [22]. This 28-item scale comprises several subdomains, including disinhibition, awareness, external cues, emotional response, and distraction. Scores range from 0 to 4, with higher scores indicating greater mindful eating skills. This scale has been previously validated in adult populations [22].

##### Food Preparation Experience and Confidence Survey

This survey measures cooking self-efficacy and frequency of use of 13 different cooking styles (eg, boiling, baking, and microwaving). Participants are asked to rate their perceived confidence of each cooking method, ranging from confident, to uncertain, to not confident. This survey has been validated among young adults [23].

##### Body Appreciation Scale

Body appreciation reflects positive body image and has been previously associated with higher levels of self-esteem and lower levels of coping by avoidance. The Body Appreciation Scale is composed of 13 items, to which participants are asked in a Likert format the frequency to which they exhibit each statement [24]. Examples of statements on the questionnaire include “I respect my body” and “I do not focus a lot of energy being concerned with my body shape or weight.” Scores range from 1 to 5, with higher scores indicating higher levels of body appreciation. This scale has been validated among young adults [24].

##### Weight Satisfaction

Weight satisfaction is measured using 3 items. The first asks, “Which of the following are you trying to do about your weight?” This gives respondents the ability to state that they are trying to lose weight, gain weight, stay the same weight, or that they are not doing anything about their weight. The second item measures how they feel about their current weight, with responses including “happy,” “upset,” or “don’t care.” The third item inquires about their desired weight in pounds. Weight satisfaction is then determined using the formula: [(actual weight – desired weight)/actual weight × 100].

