### MasterChef Analysis

MasterChef will be evaluated initially for feasibility through a qualitative focus group design along with an expert content analysis. After modifications to the program based on feasibility analysis, the intervention will be evaluated using a matched-based cohort design with the non-MasterChef control group selected based on gender, ethnicity, and year in college matched-based design, with a focus on gender, ethnicity, and year in college. Descriptive and frequency statistics were used to analyze the sample’s baseline and demographic data. A 2-way repeated-measures analysis will be used to assess significant changes in baseline and postintervention outcomes within the experimental group and as a comparison with the control. Participants will complete the aforementioned nutrition measures before the week-long Fall 2023 program delivery, directly after the program, and again at the end of the semester. A control will be recruited through a matched-based design. A 2-way repeated-measures ANOVA will be used to identify significant changes between baseline data, postintervention data, and follow-up data between the intervention and control group. The program will also be implemented in the format of monthly workshops. A multivariate ANOVA will be used to compare health outcomes between curriculum formats. Multiple linear regressions will be used to identify predictors of diet quality using the combined fall and spring samples. Significance levels will be set at *P*<.05.

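### The weight-satisfaction formula is signed, so it scores direction and size of desired weight change rather than satisfaction, and opposite signs cancel in a group mean

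*Protocol article*

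**What the plan says.** Under Nutrition Assessments, the Weight Satisfaction section describes three items. The first lets respondents say they are "trying to lose weight, gain weight, stay the same weight", or taking no action. The second asks how they feel about their present weight (happy, upset or indifferent). The third asks for desired weight in pounds. The section then fixes the score: "Weight satisfaction is then determined using the formula: [(actual weight – desired weight)/actual weight × 100". It gives no absolute value, no separate scoring for losing and gaining, and no statement of what a high value means. The article does say what higher scores mean for the Mindful Eating Questionnaire, the Body Appreciation Scale and the Short Healthy Eating Index.

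Under MasterChef Analysis the article says: "Participants will complete the aforementioned nutrition measures before the week-long Fall 2023 program delivery", with repeats just after delivery and at the end of the semester. The stated comparison is: "A 2-way repeated-measures ANOVA will be used to identify significant changes between baseline data, postintervention data, and follow-up data between the intervention and control group". That section does not mention weight satisfaction by name, or any split by the direction in which participants want their weight to change.

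**The concern.** A satisfaction score should move one way as satisfaction rises. This one does not. Above zero, a larger value means a wider gap and so less satisfaction. Below zero, a larger value means a narrower gap and so more. The first item shows that the authors expect wishes in both directions, so both signs should be expected.

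A repeated-measures ANOVA compares group means over time. If the signed score is averaged across people who want to lose and people who want to gain, their values offset each other. A real narrowing of gaps could then look like little or no change, or like a change in the wrong direction. At stake is whether the weight-satisfaction result for MasterChef can be interpreted.

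**Working it through.** **Inputs.** The formula comes from the Weight Satisfaction section. The article gives no mean, gap size, gain share or sample size for this measure, so there is no figure of its own to reproduce. The following are assumptions for illustration: actual weight 150 lb, a gap of 10% in either direction, and a gain share p of 0 to 50% among those with a gap.

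**Step 1: individual scores.** Score = (actual − desired)/actual × 100.
- Desired 135 lb: (150 − 135)/150 × 100 = +10
- Desired 165 lb: (150 − 165)/150 × 100 = −10
- Desired 150 lb: 0

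One person at +10 and one at −10 average 0, the same as two people with no gap. A person who moves from +5 to −5 changes by 10 points although the size of the gap is the same.

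**Step 2: group means at one time.** Let s be the share with a gap and g the gap size. Signed mean = s × g × (1 − 2p). Absolute mean = s × g. With s = 0.8 (20% content) and g = 10:

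| Gain share p | Signed mean | Absolute mean |
|---|---|---|
| 0 | 8.0 | 8.0 |
| 0.1 | 6.4 | 8.0 |
| 0.2 | 4.8 | 8.0 |
| 0.3 | 3.2 | 8.0 |
| 0.4 | 1.6 | 8.0 |
| 0.5 | 0.0 | 8.0 |

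**Step 3: every gap halves.** Everyone starts with a 10% gap (s = 1) and ends at 5%. Signed change = −5 × (1 − 2p). Absolute change = −5.

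| Gain share p | Signed change | Absolute change |
|---|---|---|
| 0 | −5 | −5 |
| 0.2 | −3 | −5 |
| 0.3 | −2 | −5 |
| 0.5 | 0 | −5 |

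**Step 4: only those wanting to gain close their gap.** Take p = 0.3 and a 10% gap for everyone at the start.
- Signed mean before: 0.7 × 10 − 0.3 × 10 = 4. After: 0.7 × 10 + 0 = 7. Change +3.
- Absolute mean before: 10. After: 0.7 × 10 = 7. Change −3.

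The gaps have narrowed, yet the signed mean has moved the way it would if people who want to lose had become less satisfied.

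**Step 5: a case where the absolute score is blind.** Take equal groups. Those wanting to lose go from +10 to +15, and those wanting to gain go from −10 to −5.
- Signed mean: 0 before, 0.5 × 15 − 0.5 × 5 = 5 after.
- Absolute mean: 10 before, 0.5 × 15 + 0.5 × 5 = 10 after.

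Here the signed score shows the shift and the absolute score does not, so neither is sufficient alone when pooled.

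**The case against.** The strongest reply is that the article defines an individual score and never says it will be averaged across directions. MasterChef Analysis does not name weight satisfaction. Its sentence on the nutrition measures concerns data collection, and two of the three weight items are categorical and could not enter the ANOVA as they stand. A split by direction could be in a fuller document that is not shown. This stands in part: the pooled mean is an inference. It is nevertheless the natural reading, because the nutrition measures are taken at three times and the only stated group comparison over time is the repeated-measures ANOVA. The scoring rule and its label are printed in full, and their mismatch does not depend on that inference.

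A second reply is that no information is lost. The signed value can be converted to an absolute one later but not the reverse, and the first two items already record direction and feeling. This is correct. It makes the problem easy to repair, but it does not make the printed score a measure of satisfaction.

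A third reply is that the absolute value has a cost of its own: it drops direction, as Step 5 shows. This stands. For the same reason, a reader might infer that the signed score would conceal a growing wish to be lighter in one subgroup. It need not: in Step 5 the signed score reveals exactly that shift.

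**Conclusion.** The point holds. The printed formula yields a signed desired-change score under the label of weight satisfaction. Zero means no gap, and values further from zero on either side mean less satisfaction.

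The effect on the ANOVA is conditional on the signed score being analysed as a pooled group mean. Its size depends on the share wanting to gain. With equal gap sizes in both directions there is no distortion if nobody wants to gain and complete cancellation if the gaps balance. At p = 0.3 a uniform 5-point improvement appears as 2 points, and a change confined to those wanting to gain appears with the opposite sign. These figures rest on the assumed gaps and shares.

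A reader might infer that the MasterChef weight-satisfaction result will be attenuated by a known amount. The article supplies no gain share or gap distribution, so that cannot be said. Nor does the point reach the study's main questions. Weight satisfaction is one of five nutrition instruments in one sub-intervention, and nothing here affects the burnout, resilience or stress outcomes.

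**What to change.** 1. Define a weight-discrepancy (dissatisfaction) score as |actual − desired|/actual × 100, state that 0 means no gap and higher means less satisfied, and use it for the satisfaction comparison in the repeated-measures ANOVA. Under the Step 1 assumptions, 135 lb and 165 lb both score 10.
2. Keep the signed value under a name that describes it, such as desired weight change. Report it separately for those wanting to lose, those wanting to gain and those wanting neither, using the first item.
3. Use the second item as a direct check that a larger discrepancy goes with less satisfaction.
4. State in MasterChef Analysis which of these quantities enters the ANOVA.

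The cost is a changed line of scoring code, one extra summary by direction and a sentence or two of text. All the data are already collected. The trade-off is that the absolute score alone hides changes of direction, so items 1 and 2 of this list belong together.
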